### Case Report Forms

Forms are provided .

## DATA SUBMISSION - CASE REPORT FORMS SCHEDULE

| Form code | Type of Form                                  | Schedule                                                        |
|-----------|-----------------------------------------------|-----------------------------------------------------------------|
| FORM 1    | Verification of eligibility and Randomization | To fill in before randomization procedure                       |
| FORM 2    | Medical history                               | To fill in within two month from date of surgery                |
| FORM 3    | Axillary ultrasound/ Fnac                     | To fill in within two month from date of surgery                |
| FORM 4    | Surgery                                       | To fill in within two month from date of surgery                |
| FORM 5    | Suggested adjuvant therapy                    | To fill in within two month from date of surgery                |
| FORM 6    | Follow-up                                     | To fill in every six months for five years from date of surgery |

## **PROPERTY OF DATA AND PUBLICATION POLICY**

Property of data is of European Institute of Oncology.

The main results of the clinical trial will be published in a peer-reviewed scientific journal. The final publication will be written by the Principal Investigator on the basis of the final analysis performed by the European Institute of Oncology Statistical Center.

Co-authors will be co-investigators of the study who participate in the design and drawing up of the research project, a representative of the European Institute of Oncology Statistical Center, a representative of the European Institute of Oncology Data Management and at least one representative of each participating center. Other persons who significantly contributed to data collection, analysis, or manuscript drawing might be considered as Co-authors.

All publications, abstracts or presentations including data related to the present trial will be submitted for review to the Principal Investigator prior to submission.

## **LIST OF ABBREVIATIONS**

|      |                               |
|------|-------------------------------|
| SLN  | Sentinel lymph node           |
| SLNB | Sentinel lymph node biopsy    |
| DDFS | Distant disease-free survival |
| DFS  | Disease-free survival         |
| OS   | Overall survival              |
| IQR  | Interquartile range           |
| RCT  | Randomized clinical trial     |

## 1. STUDY OBJECTIVES

### 1.1. PRIMARY OBJECTIVE

To verify whether, in patients with small breast cancer, and in presence of a negative preoperative axillary assessment, SLN can be spared without worsening the prognosis

### 1.2. SECONDARY OBJECTIVES

To verify whether, in presence of a negative preoperative axillary assessment, the decision on adjuvant medical treatment can be taken according only to the biology of the tumour without the prognostic information achieved by SLNB on the nodal status

To verify whether, in presence of a negative preoperative axillary assessment, the decision on adjuvant medical treatment can be taken according only to the biology of the tumour without the prognostic information achieved by SLNB on the nodal status

## 2. BACKGROUND/INTRODUCTION

### 2.1. STUDY DESIGN

Study design: Prospective randomized controlled non-inferiority trial

Number of centres: 18

Number of Countries: 4

Accrual period for the experimental study phase: 5 years (2012-2017)

Additional follow-up years after the last entry: 5 years (until 2022)

### 2.2. TREATMENT GROUPS

Two treatment groups:

1. SLNB ± axillary dissection
2. No axillary surgical staging

In the arm 1, no axillary dissection will be performed in case of either negative SLN or in presence of isolated tumour cells or micrometastases. SLNB will be completed by axillary dissection in presence of macrometastases diagnosed in the SLN

### 2.3. STUDY POPULATION

Patients with small breast cancer (T<2 cm), with a negative preoperative assessment of the axilla (ultra-sound with FNAC in presence of doubtful findings)

## 2.4. SAMPLE SIZE

Women with pT1 tumours and negative axillary ultrasound will be randomized to receive either SLNB or no treatment in the axilla. We will consider women who will undergo SLNB as the reference group, and we will test for non-inferiority the group of women not undergoing any treatment in the axilla. The primary endpoint will be distant disease-free survival (DDFS) after randomization, with distant metastases and deaths from all causes counted as failures. For the purpose of sample size calculation, the 5-year DDFS in the reference group is assumed to be 96.5%. This estimate was obtained from the analysis of 2218 women with pT1, cN0, M0 tumours who underwent surgery (with SLNB) at the European Institute of Oncology from 01/01/2003 to 31/12/2005.

Overall, 1560 women (780 per arm) will be enrolled to decide whether the group without treatment of the axilla is no worse than the reference group, given a margin  $\alpha$  of non-inferiority of 2.5% (maximum tolerable 5-years DDFS = 94% ). Statistical power and one-sided type I error are set to 80% and 5%, respectively.

## 3. POPULATIONS OF ANALYSIS

Women with the following characteristics will be included: breast cancer <2 cm, and a clinically negative axilla, any age, candidates to receive breast conserving surgery + radiotherapy, negative preoperative assessment of the axilla, signing the written informed consent

Women will be excluded for the following reasons: withdrawal of informed consent, benign or in situ tumours, distant metastasis at diagnosis, bilateral breast tumour, previous invasive tumour

## 4. OUTCOME VARIABLES

### 4.1. PRIMARY OUTCOME

DDFS, with distant metastases and deaths from all causes counted as failures [1]. If a patient has simultaneous locoregional recurrence and distant metastasis, she will be considered as having a distant metastasis in the analysis. Ipsilateral breast cancer recurrences, regional recurrences (recurrences in the axillary lymph nodes or other regional lymph nodes), contralateral breast cancers and non-breast primary tumours will be considered as censoring events. Only the data on the first event will be used.

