The primary endpoint will be the DDFS, defined as the time free of both distant recurrence and death from any cause. If a patient have simultaneous locoregional and distant recurrences, she will be considered as having a distant recurrence in the analysis. Local recurrences, regional recurrences, contralateral breast cancers and other non-breast primary tumours will be considered as censoring events. The log-rank test will be used to test differences in DDFS. Secondary endpoints will be the cumulative incidence of distant recurrences, the cumulative incidence of axillary recurrences, the disease free survival (DFS) and the overall survival (OS). Differences in the cumulative incidence will be evaluated in a competing risk framework (15) by means of the Gray test (16), while differences in DFS and OS will be evaluated by means of the Log-rank test. Multivariable Cox regression models will be applied to adjust the risk estimates of interest for other variables. The Chi-square test for trend, Chi-square test and the Fisher exact test will be used to evaluate

differences in percentages between the two treatment groups, as appropriate. The T-tests will be used to evaluate differences in means for continuous variables.

All analyses will be carried out with the SAS software (SAS Institute, Cary, NC) and the R software (The R Development Core Team 2004; Free Software Foundation, Boston, MA). All tests will two-sided. The calculation of sample size was carried out using PASS software, based on method given in Jung SH et al. (17).

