### 4.2. SECONDARY OUTCOMES

- DFS, where all collected events (i.e. ipsilateral breast cancer recurrences, regional recurrences (recurrences in the axillary lymph nodes or other regional lymph nodes), distant metastases, contralateral breast cancers, non-breast primary tumours, and deaths from all causes) will be considered as events of interest. Only the data on the first event will be used.
- OS, where deaths from all causes will be considered as events of interest. Only the data on the first event will be used.

- Cumulative incidence of distant metastases, where events different from distant metastases will be treated as competing events in a competing risk framework.
- Cumulative incidence of recurrences in axillary lymph nodes, where events different from recurrences in axillary lymph nodes will be treated as competing events in a competing risk framework.
- Final surgical treatment and recommended adjuvant therapy.

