#### **SENSITIVITY ANALYSES**

We will compare women assigned to SLNB and those assigned to omission of SLNB using an intention-to-treat approach. However, for the main endpoint, we will also report the per-protocol analysis, where women assigned to SLNB who did not receive SLNB will be excluded, as well as women assigned to omission of SLNB who receive SLNB.

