### **5.2. DATA ANALYSIS**

A description of first events, deaths and follow-up time will be provided in Table 2. Frequencies and percentages will be used to describe first events and deaths, while median with IQR will be used to describe follow-up time.

Survival curves will be estimated using the non-parametric Kaplan-Meier method (DDFS, DFS and OS). Differences in survival will be tested using the Log-Rank test, and the p-value of the test will be reported. Cumulative incidence of distant metastases and of axillary recurrences will be calculated in a competing risk framework: events other than distant metastases or axillary recurrences, respectively, will be treated as competing events. Differences in the cumulative incidence between arms will be evaluated by means of the Gray test, and the p-value of the test will be reported. For the analysis of DDFS, DFS and cumulative incidences, only the data on the first event will be used.

We will use multivariable survival models only if substantial differences in the distribution of baseline characteristics are observed. The univariate analysis will be considered as the main analysis in any case. We will possibly use multivariable Cox models if the proportionality assumption is verified. We will possibly use parametric accelerated failure time regression models if the proportionality assumption is not verified; different distributions will be tested, and the most appropriate will be chosen based on the Akaike's information criterion.

To evaluate the primary hypothesis of non-inferiority in DDFS, we will report the p-value for non-inferiority calculated at five years, based on the pre-specified margin of non-inferiority of 2.5%. This means that observations will be right-censored at five years to evaluate the primary hypothesis. With the assumptions specified in the sample size paragraph, non-inferiority is defined as a hazard ratio (HR) of less than 1.74 for no SLNB versus SLNB. Analyses will be performed using SAS software, version 9.4 (SAS Institute Inc., Cary, NC, USA). All tests will be two-sided.

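### DDFS is analysed with censoring at locoregional, contralateral and second-primary events, so distant metastases and deaths that follow them are not counted, contrary to its own definition; if regional failure is commoner or does worse without SLNB, the primary test leans towards non-inferiority

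*Supplement*

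**What the plan says.** SAP 4.1 sets the primary outcome as "DDFS, with distant metastases and deaths from all causes counted as failures". The latest protocol, in its sample size and statistical considerations section, describes DDFS as "defined as the time free of both distant recurrence and death from any cause".

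Both documents then add a censoring rule. In the protocol: "Local recurrences, regional recurrences, contralateral breast cancers and other non-breast primary tumours will be considered as censoring events". In SAP 4.1 the list includes ipsilateral recurrence and "regional recurrences (recurrences in the axillary lymph nodes or other regional lymph nodes"), and it continues "contralateral breast cancers and non-breast primary tumours will be considered as censoring events. Only the data on the first event will be used". SAP 5.2 repeats the restriction: "For the analysis of DDFS, DFS and cumulative incidences, only the data on the first event will be used". The one exception is a distant recurrence found at the same time as a locoregional one, which counts as distant.

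The only further analysis that SAP 5.1 names for this endpoint is per-protocol: "for the main endpoint, we will also report the per-protocol analysis". Overall survival is handled differently: "OS, where deaths from all causes will be considered as events of interest".

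**The concern.** The definition and the rule cannot both hold. Take a woman with an axillary recurrence in year 2 and distant metastasis or death in year 3. By the definition she fails in year 3; by the rule she leaves the risk set in year 2 as a non-failure. A woman who dies of a second primary cancer is treated in the same way, although deaths from all causes are said to count.

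The censoring happens after randomisation, may depend on arm, and is informative, because women with a recurrence or a new cancer do not have the same later risk as those without. For regional recurrence it also falls on a path that matters here: an unstaged axilla, then axillary failure, then distant spread. In a non-inferiority trial, a rule that drops events along a path of harm can make the arms look more alike than they are. The protocol justifies DDFS as a proxy for overall survival, yet the rule discards deaths that overall survival would count.

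**Working it through.** **1. The plan's own figures.** Reference 5-year DDFS is 96.5% and the tolerable limit 94% (SAP 2.4). On the hazard ratio scale the margin is ln(0.94)/ln(0.965) = 1.737, which agrees with the 1.74 in SAP 5.2. With one-sided 5% error and 80% power, the events needed are 4(1.645+0.842)²/(ln 1.737)² ≈ 81.2. The mean event probability with 5 years' accrual and 5 years' further follow-up is 0.0520, so N = 81.16/0.0520 ≈ 1561, against 1560 in the plan.

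**2. How much the rule can hide.** Use a three-state model with constant hazards: event-free; a non-distant first event (hazard ρ); distant metastasis or death (hazard λ directly, μ after a non-distant event). The 5-year DDFS as defined is

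S = e^(-5(λ+ρ)) + ρ[e^(-5(λ+ρ)) − e^(-5μ)]/(μ−λ−ρ).

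The rule as written estimates only the direct hazard λ. I set λ equal in both arms, at -ln(0.965)/5 = 0.007125 per year, so the censored analysis gives HR 1.00 in every row below.

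Assumptions not in the documents: other non-distant first events 4% at 5 years in both arms; μ of 0.1 to 0.2 per year; the axillary rates shown, converted by -ln(1−p)/5.

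| 5-year axillary recurrence, SLNB vs none | Hidden deficit, μ = 0.1 | Hidden deficit, μ = 0.2 |
|---|---|---|
| 0.9% vs 1.6% | 0.13 points | 0.24 points |
| 1% vs 3% | 0.38 points | 0.68 points |
| 1% vs 6% | 0.95 points | 1.70 points |

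Worked case, 1% vs 6%, μ = 0.2. SLNB arm: ρ = 0.00201+0.00816 = 0.01017, S = 0.9171+0.0306 = 0.9477. No-SLNB arm: ρ = 0.01238+0.00816 = 0.02054, S = 0.8708+0.0599 = 0.9308. The difference is 1.70 points. Lowering λ so that the SLNB arm is exactly 96.5% changes this row only to 0.98 and 1.75 points.

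**3. Upper bound on false non-inferiority.** Put the true 5-year DDFS at the margin, 96.5% vs 94.0%, and let a share m of the excess follow a censored event. The HR seen is 1+0.737(1−m), and the chance of claiming non-inferiority is Φ[(ln 1.737 − ln HR)/SE − 1.645], with SE from the expected 5-year events in 780 per arm.

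- m = 0: events 27.3 and 46.8, SE 0.241, chance 5%.
- m = 50%: HR 1.368, events 27.3 and 37.1, SE 0.252, chance 24%.
- m = 100%: HR 1.00, events 27.3 and 27.3, SE 0.271, chance 65%.

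For a test of the 2.5-point risk difference the same three cases give 5%, 34% and 85%. These figures remove no events from the SLNB arm. A simulation that does (1500 runs, 5-year horizon) gives about 55% and 48% with the rule as written, against about 5% and 4% when all events count. It needs no-SLNB axillary recurrence of about 18% (30% risk of distant metastasis or death within 5 years of the event) or 10.5% (50% risk).

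**4. Equal regional failure.** With 1% axillary recurrence in both arms and equal later risk, the HR is unbiased. Simulated power at the 5-year cut-off falls from about 65% with all events counted to 56% (30% later risk) or 48% (50%).

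**The case against.** A reader might infer that the primary test is biased towards non-inferiority as a matter of fact. The documents do not support that. The bias needs more regional failures, or worse outcome after them, without SLNB; with equal rates and equal later risk the rule costs power, which works against a non-inferiority claim. Contralateral and non-breast primaries have no evident reason to differ by arm.

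A reader might also take 65% or 85% as the expected error. They apply only if the whole margin-sized excess follows a censored event. The protocol names another route of harm, the loss of nodal information for adjuvant decisions, and distant metastasis arising that way as a first event is counted. The axillary rates in the protocol's introduction are 0.9% after negative SLNB, 1.6% with sentinel micrometastases and no axillary surgery, and 0.9% with positive sentinel nodes and no dissection. All those women had SLNB, so the figures are indirect, but 6% is almost four times the highest of them.

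Nor can it be said that the Kaplan-Meier estimate is incomparable with 96.5%: the documents do not state how that cohort analysis treated earlier locoregional events. And the harm is not wholly out of sight. Axillary recurrence has its own cumulative incidence and Gray test, regional recurrences count in DFS, and later deaths count in OS.

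All of this limits the size and certainty of the bias. It does not remove the contradiction. OS is secondary, has no stated margin and misses distant disease without death. The cumulative incidence of distant metastases has the same gap, because other first events compete with it.

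**Conclusion.** The point holds in conditional form. As written, DDFS omits distant metastases and deaths that follow a locoregional, contralateral or second-primary event, in conflict with its definition in both documents, and no planned sensitivity analysis of the primary endpoint restores them. The direction is towards non-inferiority if regional failure is commoner or does worse without SLNB, a harm this trial exists to exclude; otherwise the main cost is lost events and power. On the assumed later hazard of 0.1-0.2 per year, the effect runs from about 0.1-0.2 points near the documents' indirect axillary rates, where it is small against the 2.5-point margin, to 1.0-1.7 points at 1% vs 6%. The documents give no axillary rate for women without SLNB, so they cannot settle where in that range the trial lies. That is reason enough not to let the primary analysis rest on the rule.

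**What to change.** In SAP 4.1 and 5.2 and in the protocol's statistical section, define DDFS as time from randomisation to the first distant metastasis or death from any cause, regardless of any intervening locoregional recurrence, contralateral breast cancer or second primary. Censor only at last contact or the five-year cut-off, and lift the first-event restriction for DDFS. Keep the current first-event version as a prespecified sensitivity analysis.

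The cost is modest but goes beyond wording. Deaths are already needed for OS, and the follow-up form is scheduled every six months for five years with no stated stop at a first event. Its contents are not shown, however, and SAP 5.2 tabulates only first events and deaths. Dates of distant metastasis after a first event may therefore have to be retrieved from the 18 centres. The SAP is dated 1 October 2022, at the end of planned follow-up, so the change should be made, dated and justified before the data are analysed.

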### 4.2. SECONDARY OUTCOMES

- DFS, where all collected events (i.e. ipsilateral breast cancer recurrences, regional recurrences (recurrences in the axillary lymph nodes or other regional lymph nodes), distant metastases, contralateral breast cancers, non-breast primary tumours, and deaths from all causes) will be considered as events of interest. Only the data on the first event will be used.
- OS, where deaths from all causes will be considered as events of interest. Only the data on the first event will be used.

- Cumulative incidence of distant metastases, where events different from distant metastases will be treated as competing events in a competing risk framework.
- Cumulative incidence of recurrences in axillary lymph nodes, where events different from recurrences in axillary lymph nodes will be treated as competing events in a competing risk framework.
- Final surgical treatment and recommended adjuvant therapy.

### 4.3. OTHER PARAMETERS

#### DEMOGRAPHY AND BASELINE

These characteristics will be reported in Table 1:

- Age at surgery (both in categories <40, 40-49, 50-64,  $\geq 65$  and mean with IQR)
- Menopausal status (pre vs. peri/post)
- Histotype (ductal, lobular, tubular, other)
- Size of largest diameter (both in categories pT1mic and pT1a, pT1b, pT1c, pT2 and mean with IQR)
- Number of positive SLNs (SLNB not performed, 0, 1-3, 4-9, 10+)
- pN (pNX, pNSentNeg, pNSentNeg(i+), pN1mi, pN1, pN2)
- Tumor grade (I, II and III)
- ER status (negative, positive)
- PgR status (negative, positive)
- Ki-67 index (both in categories <20%,  $\geq 20\%$  and mean with IQR)
- HER2 status (Not overexpressed, overexpressed)
- Molecular subtype (luminal A, luminal B HER2 -, luminal B HER2 +, HER2 non luminal, triple negative). To define molecular subtype we used the following criteria: luminal A (positive for ER and/or PgR, negative for HER2, Ki-67 index < 14%; luminal B HER2 - (positive for ER and/or PgR, negative for HER2, Ki-67 index  $\geq 14\%$ ; luminal B HER2+ (positive for ER and/or PgR, positive for HER2); HER2+ (negative for ER and PgR, positive for HER2); and triple-negative (negative for ER, PgR and HER2).

Numbers and percentages of randomized and included participants by centre will be presented in the supplementary material. Final surgical treatment and recommended adjuvant therapy will also be presented in the supplementary material.

## 5. STATISTICAL METHODOLOGY

### 5.1. GENERAL METHODOLOGY

Frequencies and percentages will be used to describe categorical baseline characteristics, while means and IQR will be used to describe continuous baseline characteristics. Variables with

missing values will be indicated in the table. Variable distributions will be presented separately by treatment group but, since this is a RCT differences, differences between the two groups will not be tested with statistical tests, such as chi-square or T-test.

Final surgical treatment and recommended adjuvant therapy will be presented separately by treatment group, and differences will be tested using the Chi-square test.

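### The adjuvant-decision objective asks whether nodal status is dispensable, but recommended adjuvant therapy is analysed only by a whole-arm chi-square test, with no interval and no tumour-biology variable

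*Supplement*

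**What the plan says.** SAP section 1.2 states the secondary objective as whether "the decision on adjuvant medical treatment can be taken according only to the biology of the tumour without the prognostic information achieved by SLNB". The protocol's Trial Objectives section lists the same aim.

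SAP section 4.2 names recommended adjuvant therapy, together with final surgical treatment, as a secondary outcome. Section 5.1 gives its whole analysis: "Final surgical treatment and recommended adjuvant therapy will be presented separately by treatment group, and differences will be tested using the Chi-square test". Section 4.3 places the result in the supplementary material. Section 5.2 adds "All tests will be two-sided". No significance level is stated for secondary outcomes.

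For the baseline table, section 4.3 collects menopausal status, pN and "Molecular subtype (luminal A, luminal B HER2 -, luminal B HER2 +, HER2 non luminal, triple negative"). None of these enters the analysis of recommended therapy. The SAP names no therapy categories, effect estimate, confidence interval or margin for this outcome. The protocol's statistical section adds only general tests for percentages (chi-square, chi-square for trend, Fisher exact).

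**The concern.** The objective is a claim that nodal information can be done without. The planned test looks for a difference. If it is not significant, the trial has not shown that recommendations are the same. If it is significant, a p-value does not say how much changed or in which women. For DDFS the SAP handles the same logical problem properly, with a margin of 2.5 points and a hazard-ratio limit of 1.74. It offers nothing comparable here.

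The objective also turns on tumour biology, yet the analysis pools all subtypes. If nodal status matters for the recommendation in some biological groups and not in others, the pooled comparison averages over them. A reader would then not know how large a change in recommendations the data exclude, or where a change is concentrated.

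**Working it through.** **Inputs from the documents.** SAP 2.4: "Overall, 1560 women (780 per arm) will be enrolled"; "Statistical power and one-sided type I error are set to 80% and 5%, respectively"; "the 5-year DDFS in the reference group is assumed to be 96.5"%; "maximum tolerable 5-years DDFS = 94"%. SAP 2.1: 5 years of accrual and 5 further years of follow-up.

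**The plan's own figure.** No power is stated for recommended therapy; the sample size comes from DDFS, and it reproduces.
- Hazard-ratio limit = ln(0.94)/ln(0.965) = 1.737.
- Events = (1.645 + 0.842)² / (0.25 × [ln 1.737]²) = 81.2.
- Event probability under equal exponential hazards, with uniform accrual over 5 years and 5 more years of follow-up, = 0.0520.
- N = 81.2/0.0520 ≈ 1561 (1578 if events are first rounded up to 82), against 1560 stated.

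So 780 per arm is a fair basis for what follows.

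**Assumptions not in the documents.**
- One therapy, scored yes or no.
- Therapy rate b without nodal information: 20%, range 5% to 50%.
- Node-positive share f in the SLNB arm: range 5% to 20%.
- Shift s in the recommendation among node-positive women: range 10 to 50 points.
- Two-sided 5% level.
- Only a positive node changes a recommendation, and always in the same direction.

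Under the last assumption the whole-arm difference is d = f × s. For example, 10% × 30 points = 3 points.

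**Power of the planned test.** With n = 780 per arm, p̄ the mean of the two proportions, SE0 = √[2p̄(1−p̄)/n] and SE1 = √[(p1(1−p1) + p2(1−p2))/n], power = Φ((d − 1.96·SE0)/SE1) plus the small opposite tail.

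| Rates | d (points) | SE0 | Power |
|---|---|---|---|
| 20% vs 21% | 1 | 0.0204 | 8% |
| 20% vs 22% | 2 | 0.0206 | 16% |
| 20% vs 23% | 3 | 0.0208 | 30% |
| 20% vs 24.5% | 4.5 | 0.0211 | 57% |
| 20% vs 26% | 6 | 0.0213 | 80% |

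**How far this moves with the inputs.**
- f = 10%, s = 30 points: 22% to 67% as b runs from 50% down to 5%.
- f = 15%, s = 40 points: 66% (b = 50%) to 99% (b = 5%).
- f = 20%, s = 50 points, b = 5% (5% vs 15%): over 99%.
- f = 5%, s = 10 points, b = 50% (50% vs 50.5%): about 5%.

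Power therefore runs from about the test's own error rate to near certainty.

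**What an interval would show.** With 20% in both arms, the 95% half-width is 1.96 × √(2 × 0.20 × 0.80/780) = 4.0 points; it is 3.0 points at a 10% rate and 5.0 at 50%. On the same assumptions with f = 10%, an observed arm difference of zero is still compatible with 4.0/0.10, or about 40%, of node-positive women having their recommendation changed. A bare p-value does not show this.

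**The case against.** **The question is also framed through outcome.** The protocol's hypothesis is that lacking nodal information does not worsen outcome, and DDFS non-inferiority tests that against a margin. Recommendations could differ and outcome still be no worse. This stands, and it limits the point: DDFS answers whether outcome suffers, not whether or where recommendations changed. The therapy outcome is there for the latter.

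**Percentages by arm are presented anyway.** This also stands. Their difference estimates the net effect of omitting SLNB, and an interval could be worked out from the counts. What is missing is a planned interval, a limit to judge it by, and any split by biology.

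**The whole-arm contrast is the valid randomised one.** Correct. Women without SLNB are pNX, so node-positive women cannot be compared between arms. The remedy has to keep the randomised contrast.

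**The product f × s is an assumption, not an identity.** A confirmed negative node, as against an unknown one, could also change a recommendation. That could raise or lower the arm difference, so the power figures are illustrations only.

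**Two stronger readings are tempting.** A reader might infer that the test will usually be non-significant. The documents give no node-positive share, therapy rate or size of change, and the range above shows the inference fails for some plausible inputs. A reader might also infer that the trial will declare biology sufficient on a non-significant result. The SAP contains no such rule and does not expressly tie this test to the objective.

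**Conclusion.** The point holds as a gap between objective and analysis. A named secondary objective claims that nodal information is dispensable, and the only planned analysis of its matching outcome is a difference test that cannot support such a claim and uses no biology variable. This follows from the text of the SAP and needs no numerical assumption.

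The size is illustrative. At an assumed 20% rate and 780 per arm, differences of 1 to 4.5 points have about 8% to 57% power, and about 6 points are needed for 80%; other inputs give over 99%. The primary DDFS conclusion is not affected. The change is worth making because the data are already collected.

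**What to change.** In SAP 5.1, for recommended adjuvant therapy:

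1. Name the therapies (chemotherapy, endocrine, anti-HER2, radiotherapy). For each, report the randomised between-arm difference in percentage with a 95% confidence interval.
2. Repeat this within the molecular subtypes and menopausal groups of section 4.3, labelled exploratory.
3. Add a table of recommendation by pN within the SLNB arm, labelled descriptive and non-randomised, since pN may go together with other features that drive the recommendation.
4. State that the conclusion rests on the size of difference the interval excludes, judged against a limit set before analysis, and not on a non-significant p-value. The chi-square p-value may stay alongside.

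The cost is one extra table from data already collected. Four therapies across five subtypes and two menopausal groups give up to 4 × (5 + 2) = 28 exploratory intervals, so no single one should be read as confirmatory. Small subtypes will be imprecise: for a subtype assumed to hold 10% of each arm (78 women) at a 20% rate, the half-width is 1.96 × √(2 × 0.20 × 0.80/78) = 12.6 points.
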